### Primary outcome measures

The primary outcome measure of the PORTAL trial for all participating patients is time to postoperative functional recovery, measured in days. The patients’ postoperative course will be evaluated daily by the nursing and medical staff and will be communicated to the study coordinators for documentation. Postoperative criteria that need to be fulfilled independently to achieve functional recovery status are as previously described [18]:
Discontinuation of intravenous or subcutaneous analgesia and preservation of adequate control levels (assessed by a pain score).Ability to maintain sufficient oral caloric intake as defined by the institutional dietetic services (no less than 50% of recommended dietary intake), without intravenous fluid support.Restoration of patient ambulation to an independent or preoperative level if mobility deficits were present.No clinical or biochemical signs of ongoing abdominal infection affecting the patient’s performance status: absence of fever and normalization of inflammatory markers (white cell count, procalcitonin, and/or C-reactive protein). Patients can be in oral antibiotics.

Additionally, in a sub-cohort of patients with pancreatic ductal adenocarcinoma assessed between the two study arms, the primary outcome will be the percentage of patients who achieve administration of adjuvant chemotherapy at 8 weeks postoperatively. The chemotherapy regimen will be decided by the oncology service on an individual basis and will not affect the comparison.

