### Statistical considerations and analysis

The main hypothesis in the PORTAL trial is that functional recovery of patients who undergo RPD is non-inferior to the one of patients who undergo OPD. Based on institutional historical data and information from retrospective series in the literature, the time to functional recovery in OPD is 10 days with a standard deviation of 2.5 days. Non-inferiority of functional recovery in RPD will be assessed with a non-inferiority (*δ*) margin of 10% or 1 day. With a one-sided test, a significance level of 5% (*α* = 0.05), and a power (1 − *β*) of 80%, the cohort for the trial is calculated to 200 patients (per-protocol (PP) group), using the PASS 11.0 software (NCSS, Kaysville, UT, USA) with a sample allocation ratio of 1:1 between the RPD and OPD groups. However, we anticipate a conversion rate in the RPD group of 10%, 3% incidence of occult abdominal metastatic disease in both groups, and 5% of patients to be lost to follow-up. Therefore, the final cohort will include 122 patients in each arm (intention-to-treat (ITT), Fig. 1). The main analysis will be conducted on the ITT group according to the randomized initial assignment of patients in each study arm at baseline. All enrolled patients from the ITT population who do not fulfill the aforementioned protocol violations will be included in the PP group. Additionally, patient characteristics of those who will be excluded from the PP analysis will be separately evaluated. Non-inferiority will be concluded if the lower bound of the 95% confidence interval (CI) for the difference between the two groups in time to functional recovery is not lower than − 1 day of the non-inferiority margin.

A second primary endpoint of the study is the percentage of patients with a diagnosis of pancreatic adenocarcinoma in each study arm, who will be fit for the initiation of postoperative adjuvant chemotherapy 8 weeks after the day of surgery. Institutional empirical data demonstrate that 50% and 75% of patients who undergo OPD and RPD, respectively, are eligible for adjuvant chemotherapy at 8 weeks, which is considered the optimal time for postoperative systemic treatment. With the same power and significance level as in the ITT group, 64 patients with pancreatic adenocarcinoma will be included in each arm to assess for the superiority of RPD.

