Primary and secondary outcome data for both ITT and PP groups will be compared utilizing appropriate statistical methodology. Categorical variables will be represented as frequency and proportion and will be analyzed using Fisher’s exact or chi-square tests, as appropriate. Continuous variables will be presented as mean values with standard deviation (SD), or median values with interquartile range (IQR), and will be compared using the two-sample *t*-test or Mann-Whitney *U* test, as per the type of distribution. A logistic regression analysis was performed for consideration of randomization stratification, based on the predetermined parameters. Survival of patients with pancreatic adenocarcinoma between the two arms will be estimated using the Kaplan-Meier analysis method and compared between the groups with the log-rank test. The SAS software v. 9.2 (SAS Institute Inc., USA) was utilized for all statistical analyses.

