This study was designed as a non-inferiority trial, and the rationale for this decision was based on the lack of robust retrospective data to demonstrate the superiority of RPD versus OPD, regarding functional recovery. The goal is to prospectively examine the outcomes in RPD and demonstrate non-inferiority of this approach compared to OPD. Furthermore, the decision to focus on RPD only and not include laparoscopic pancreatoduodenectomy patients was multifactorial: the robotic platform offers extra degrees of freedom and improved surgical ergonomics and was previously found to have an advantage compared to the laparoscopic approach [32]. Additionally, LEOPARD-2, a prospective randomized trial comparing LPD versus OPD, failed to demonstrate the superiority of LPD in functional recovery, but most importantly, the minimally invasive arm was associated with more complication-related deaths and the study was terminated early for safety purposes [6]. These results have revealed both the significance of the learning curve and surgical experience in MIS.

The number of enrolled patients in the PORTAL trial is 244 and was calculated taking under consideration three main protocol parameters: [1] conversion to open surgery in the RPD arm, which was defined as 10% based on historical institutional data [2]; intraoperative findings of occult abdominal metastatic disease; and [3] loss to follow-up, which in randomized controlled trials where included patients are closely monitored is approximately 3% [33]. The selection of eligible patients was limited to upfront resectable lesions without the involvement of major vessels. RPD with vascular resection or in patients with PDAC who previously underwent neoadjuvant are being performed in the participating institutions in increasing numbers, and recent reports have demonstrated their safety and feasibility [34, 35]. However, the technical challenges encountered in these patients would considerably affect the studied outcomes. All participating institutions are national referral centers and are considered very high volume in terms of open and robotic pancreatic surgery. Considering the number of patients that are being reviewed on a daily basis, we expect no delays in patient recruitment via an initial approach at the outpatient clinic preoperatively.

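### The observed distribution chooses the primary test, so the difference held against the 1-day margin is not fixed and may not be the mean difference on which the trial was sized

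*Protocol article*

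**What the plan says.** All of this is in the protocol article.

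- **Endpoint** (Primary outcome measures): the primary outcome "is time to postoperative functional recovery, measured in days". Four criteria must all be met: pain control without injected analgesia, oral intake, ambulation and no ongoing abdominal infection.
- **Sizing** (Statistical considerations and analysis): "the time to functional recovery in OPD is 10 days with a standard deviation of 2.5 days", with a "margin of 10% or 1 day". At the stated power "of 80%, the cohort for the trial is calculated to 200 patients", raised to 122 per arm.
- **Decision rule** (same section): the bound of a 95% "confidence interval (CI) for the difference between the two groups in time to functional recovery" is compared with minus 1 day. The kind of difference (mean, median or location shift) and the order of subtraction are not given.
- **Method** (same section, later paragraph): the paragraph opens by placing both primary and secondary outcomes, in both the ITT and PP sets, under its methods. Continuous variables "will be compared using the two-sample *t*-test or Mann-Whitney *U* test, as per the type of distribution". Kaplan-Meier and log-rank methods are named only for survival in the pancreatic adenocarcinoma patients.

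**The concern.** The margin and the sample size are on the scale of mean days. The method paragraph then lets the data decide whether the primary comparison is made on means or on ranks. The two methods estimate different quantities, so the choice also decides what is compared with 1 day, and it is made after the data are seen.

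The rank branch is the likelier one. Infection, slow return to eating and other complications delay recovery in some patients by many days, which gives a long right tail. If robotic surgery were worse because a minority of patients recover much later, the mean would register it and the rank-based shift would largely miss it. The trial could then claim non-inferiority within 1 day although mean recovery is a full day longer or more.

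**Working it through.** **1. The scale of the sizing.** Inputs from the article: SD 2.5, margin 1 day, true difference 0, power 80%.

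n per arm = 2 × SD² × (z₁₋α + z₀.₈)² / margin²

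- One-sided α = 0.025: 2 × 6.25 × (1.960 + 0.842)² / 1² ≈ 98.1, so 99 per arm. The t-distribution version gives 100 per arm, 200 in total, which is the article's figure.
- One-sided α = 0.05, as the article states: 2 × 6.25 × (1.645 + 0.842)² ≈ 77.3, so 78 per arm, 156 in total.
- Inflation: 100 / (1 − 0.10 − 0.03 − 0.05) = 100 / 0.82 ≈ 122 per arm, as stated.

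The 200 therefore comes from a difference in *means* read against a two-sided 95% interval. The mismatch with the stated 5% one-sided level is a separate matter.

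**2. What each branch estimates.** The t-test branch gives an interval for mean(RPD) − mean(OPD). The Mann-Whitney branch gives a p-value for no difference. Inverted, it gives a Hodges-Lehmann interval for the median of all pairwise differences. The two targets coincide if RPD is OPD plus a constant, and need not otherwise.

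**3. Size, by simulation.** 122 per arm; non-inferiority is declared if the upper 95% limit of RPD − OPD is below 1 day. The article does not say how the distribution is judged, so a Shapiro-Wilk test at 5% in either arm is assumed. All scenarios are assumptions.

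- *Pure shift:* OPD mean 10, SD 2.5 (normal or lognormal); RPD the same plus 1 day.
- *Tail:* OPD as above; 10% of RPD patients take 10 days longer. Mean difference = 0.10 × 10 = 1.0 day, exactly at the margin.
- *Mixture:* uncomplicated 8.5 days (SD 1.5), complicated 20 days (SD 6); 15% complicated in OPD, 25% in RPD. Means: 0.85 × 8.5 + 0.15 × 20 = 10.225 and 0.75 × 8.5 + 0.25 × 20 = 11.375; difference 1.15 days, beyond the margin.

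| Scenario | True mean difference | Rank-based shift | Non-inferiority, mean interval | Non-inferiority, rank interval |
|---|---|---|---|---|
| Pure shift, normal | 1.0 | 1.00 | 2.5% | 2.1% |
| Pure shift, lognormal | 1.0 | 1.01 | 2.6% | 2.4% |
| Tail, normal | 1.0 | 0.49 | 3.1% | 31% |
| Tail, lognormal | 1.0 | 0.46 | 3.0% | 35% |
| Mixture | 1.15 | 0.38 | 1.5 to 2.5% | 52 to 53% |

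Repeat runs with other random seeds put the rank figure for the tail scenarios between 28% and 35%, and for the mixture at 50% or a little above. In the tail and mixture scenarios the normality test rejected in practically every trial, so choosing by distribution gave the same result as always using ranks.

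**The case against.** The strongest reply is that the article does prespecify a test against the margin. The decision rule is an interval against 1 day, and the later paragraph can be read as generic description that leaves the rule untouched. This stands in part. A reader might infer that the margin would go untested, or that a non-significant Mann-Whitney result would pass as non-inferiority. The article says neither, and a rank method can supply an interval in days. The proportion of non-significant Mann-Whitney tests is also no measure of the fault: in the mixture it is about 75%, but the t-test is non-significant in 61 to 64% too. What the reply does not remove is that the interval's target is unnamed, while the only stated method for the primary outcome depends on the data.

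The mixture is also open to criticism. Its OPD SD is √(0.85 × 2.25 + 0.15 × 36 + 0.85 × 0.15 × 11.5²) ≈ 4.9, well above the planned 2.5. The tail scenario keeps OPD at 2.5 and still shows the effect, so the conclusion does not depend on the mixture.

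A further reading is tempting: neither named test can use a patient without a recovery time, so deaths would drop out and flatter the arm with more of them. The Discussion adds weight by noting of the laparoscopic trial that "the minimally invasive arm was associated with more complication-related deaths". The documents do not support stating this as fact. Nothing says deaths are excluded, the main analysis is ITT, and a condensed article may leave the rule to the full protocol or SAP. Dropping deaths favours an arm only if death or non-recovery rates differ, and mortality is reported and monitored separately.

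**Conclusion.** The point holds as a defect in what the article states, not as a detail left for later. It gives a rule for the primary outcome that lets the observed distribution choose the method, and that rule does not match the mean-based sizing and margin in the same section. An SAP that followed it would inherit the problem.

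The consequence can be large but is conditional. Where robotic surgery produces more long recoveries and the true mean difference is at or beyond 1 day, the rank branch declares non-inferiority in about 28 to 52% of trials, against about 3% or less for the mean. Where the whole distribution shifts, there is no penalty. The figures rest on the assumed tail, the assumed mixture and the assumed normality check. That recovery times will be right-skewed is an expectation from the endpoint's definition, not a figure in the article.

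The handling of patients who die or never recover is a request for clarification only.

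**What to change.** In Statistical considerations and analysis:

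1. Name one primary quantity that matches the sizing: the difference in mean days to functional recovery, RPD minus OPD, with a 95% confidence interval from robust or bootstrap standard errors, whatever the distribution. With that order of subtraction, non-inferiority means an upper limit below +1 day, so the sentence on the lower bound and −1 day should be aligned.
2. Take the primary outcome out of the paragraph that chooses tests by distribution. Keep Mann-Whitney with the Hodges-Lehmann interval as a sensitivity analysis only.
3. State, or point to where it is stated, how a patient who dies or does not recover enters this analysis. A supportive restricted-mean analysis, counting such patients at a prespecified time limit, would show whether the conclusion depends on the answer. Naming the mean difference does not by itself settle this.

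The cost is wording and one supportive analysis, with no new data or patients. The supportive analysis will probably have a wider interval. The changes should be made before anyone sees outcome data by arm.

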### Randomization process (Fig. 1)

Eligible patients will be identified and discussed about the trial at the time of initial outpatient clinic assessment. Details will be provided to the patients about the goals and the structure of the trial and how it will affect the treatment approach. Recruited patients will be informed further in detail and will sign a written informed consent prior to treatment initiation, which can be revoked at any time. After signing the informed consent, all included patients will be randomized in a 1:1 ratio between robotic and open pancreatoduodenectomy using an online randomization module (IRT, Shanhu Health, Shanghai, China). Eligible patients will be variably randomized in equal proportions, with variable sizes blocks. After enrollment, they will be randomly stratified preoperatively based on [1] risk of developing a postoperative pancreatic fistula (POPF) using an externally validated model [17]: high risk (pancreatic duct diameter < 3 mm on preoperative CT at the pancreatic neck, and/or body mass index (BMI) > 25 kg/m^2^) versus low risk (pancreatic duct diameter ≥ 3 mm on preoperative CT at the pancreatic neck, and/or BMI ≤ 25 kg/m^2^) [2]; presence of endoscopic stenting for preoperative biliary drainage; and [3] diagnosis of pancreatic adenocarcinoma. Patient randomization and allocation between the two arms is performed with dedicated software (irtlite.irtone.com); after allocation, the patient details and allocated arm are typed into sealed envelopes by the randomization team, and the clinical nurse specialists deliver the envelopes to the appropriate surgical teams. The envelopes will be opaque and numbered with the patient trial ID number and will be opened by the responsible surgical team 1 day prior to surgery. Participating patients will be blinded to the procedure until postoperative day 5 or until functional recovery is achieved. Blinding will occur with the placement of identical wound dressings in all patients: on the presumed midline or J-incision and the placed trocars sites and extraction site incision in the RPD group and on the midline or J-incision and the presumed trocar sites and extraction site incision in the OPD group (Fig. 2a). Wound changes will occur as clinically indicated in an attempt to maintain patient blinding. This is a feasible approach that has been tested in previous randomized prospective trials [6, 18]. Unblinding of participating patients will be available as per their request; if a patient is accidentally unblinded, the event will be noted, and the patient will be excluded from the per-protocol analysis.

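### Randomisation is stratified by three factors, but days to functional recovery are compared without adjustment, and the one model named for the strata is a logistic regression, which cannot give the difference in days that is judged against the 1-day margin

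*Protocol article*

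**What the plan says.** All places are in the protocol article.

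- **Randomization process:** patients are stratified before surgery by three factors. The first is risk of pancreatic fistula, high or low. The others are "presence of endoscopic stenting for preoperative biliary drainage; and [3] diagnosis of pancreatic adenocarcinoma".
- **Primary outcome measures:** the outcome for all patients "is time to postoperative functional recovery, measured in days".
- **Statistical considerations and analysis, decision rule:** "Non-inferiority will be concluded if the lower bound of the 95% confidence interval (CI) for the difference between the two groups". The bound concerns days to recovery and must stay at or above −1 day. The main analysis is by intention to treat (ITT), with 122 patients per arm.
- **Same section, tests:** the paragraph on methods covers primary and secondary outcomes together. Continuous variables "will be compared using the two-sample *t*-test or Mann-Whitney *U* test, as per the type of distribution".
- **Same section, strata:** "A logistic regression analysis was performed for consideration of randomization stratification, based on the predetermined parameters". The sentence is not tied to any endpoint.

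**The concern.** The article names a method for the strata, and that method does not fit the endpoint on which the main hypothesis rests. A logistic regression gives an odds ratio for a binary outcome. It cannot give a difference in days or an interval to hold against 1 day. The tests that are named for days carry no covariates. Read as written, the strata do not enter the comparison of recovery times.

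This matters because stratified blocks balance the three factors between the arms. If those factors predict recovery time, the true sampling error of the arm difference is smaller than an unadjusted test assumes. The test still counts the between-stratum variance in its standard error, so its interval covers more than 95% of the time. What is at stake is precision and some power. A second risk is a choice between adjusted and unadjusted results after the data are seen, should the bound fall close to the margin.

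**Working it through.** **Inputs from the article:** SD 2.5 days, margin 1 day, 1:1 allocation, 200 patients per protocol, 244 by ITT (122 per arm), decision by a 95% interval. **Assumptions:** true difference 0; R2, the share of variance in recovery time explained by the three strata, is not given and is varied from 0 to 0.20.

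**1. The plan's own sample size.** n per arm = 2 × SD² × (z₁₋α + z₀.₈₀)² / margin².

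- One-sided 2.5%, the level implied by the 95% interval: 12.5 × (1.960 + 0.842)² = 98.1, so 99 per arm. The exact t version gives 100 per arm, or 200, with power 80.4%. This reproduces the plan.
- One-sided 5%, as stated in the text: 12.5 × (1.645 + 0.842)² = 77.3, so 78 per arm, or 156. This does not reproduce the plan, so 2.5% is used below.
- Inflation for losses of 10% + 3% + 5% = 18%: 200 / 0.82 = 243.9, so 244. This reproduces the plan.

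The 200 therefore rests on the unadjusted SD of 2.5 days. It claims nothing from the strata.

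**2. Interval width at 122 per arm.** Unadjusted SE = 2.5 × √(2/122) = 0.320, so the half-width is 1.96 × 0.320 = 0.627 days. Adjusted SE = 0.320 × √(1 − R2).

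**3. Power against 1 day.** Under stratified randomisation the true SE is the adjusted one for both analyses.

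- Unadjusted power = Φ((1 − 0.627) / (0.320 × √(1 − R2)))
- Adjusted power = Φ(1 / (0.320 × √(1 − R2)) − 1.96)
- One-sided error of the unadjusted interval at the margin = 1 − Φ(1.96 / √(1 − R2))

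| R2 | Half-width, unadjusted (days) | Half-width, adjusted (days) | Power, unadjusted | Power, adjusted | Coverage, unadjusted | One-sided error, unadjusted |
|---|---|---|---|---|---|---|
| 0 | 0.627 | 0.627 | 87.8% | 87.8% | 95.0% | 2.5% |
| 0.05 | 0.627 | 0.611 | 88.4% | 89.3% | 95.6% | 2.2% |
| 0.10 | 0.627 | 0.595 | 89.0% | 90.9% | 96.1% | 1.9% |
| 0.20 | 0.627 | 0.561 | 90.3% | 93.7% | 97.2% | 1.4% |

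**4. Check by simulation.** 4,000 runs, 244 patients, eight strata, blocks of 4 and 6. At R2 = 0.20, unadjusted against adjusted: power 89.7% v 93.6%, half-width 0.630 v 0.564 days, coverage 96.7% v 94.8%, one-sided error at the margin 1.5% v 2.5%. At R2 = 0.10, power was 88.2% v 90.1%. At R2 = 0 the two analyses agreed. The formulas hold within simulation error.

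**The case against.** The best case for the plan has four parts.

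- **The size rests on an assumption.** Nothing in the article says how well the strata predict recovery time. This stands. The two fistula-risk groups are also each defined with and/or, so they overlap as written, and the prognostic value of that factor is less certain than its clinical rationale suggests.
- **No promise is broken.** This also stands. The 200 was computed with the unadjusted SD, and the unadjusted test keeps its error at or below 2.5%.
- **A condensed article may leave the covariate model to the analysis plan.** This stands only in part. The article does not say how the 95% interval is derived, and the logistic sentence could be meant for the binary chemotherapy endpoint, where it would be sound. But the article does name the tests for its primary outcomes and a model for the strata, and gives no strata-aware analysis that can produce a difference in days.
- **A linear model does not deal with skewed days, which the Mann-Whitney option allows for.** This is fair and is met in the fix. The Mann-Whitney test does not itself supply an interval for a difference in mean days.

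A reader might infer more: that the interval is certainly too wide, that a truly non-inferior robotic arm will fail more often than the design allows, or that adjustment brings about 5 points of power at R2 = 0.12. The documents do not support these. The first needs R2 above 0. The second is contradicted by the sample size calculation. The third compares adjusted power at R2 = 0.12 with unadjusted power at R2 = 0, at 100 per arm (85.1% v 80.4%, exact t). Like for like, the formulas above with SE 2.5 × √(2/100) = 0.354 give 82.3% v 85.4% at R2 = 0.12, about 3 points. A 5-point gain needs R2 near 0.19, which for two equal fistula-risk groups means a mean difference of √(0.19 × 6.25 / 0.25) = 2.2 days. The main analysis is also at 122 per arm, where the gain is smaller.

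**Conclusion.** The mismatch is real. The strata that govern allocation have no stated role in the comparison of recovery times, and the one model named for them cannot give a result in days.

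The cost is conditional and modest. At the ITT size the half-width would shrink by about 2.5%, 5% and 11% at R2 of 0.05, 0.10 and 0.20, and power would rise by about 1, 2 and 3 points. At R2 = 0 there is no loss. The error is on the conservative side: type I error is not inflated, and power stays above the planned 80%. These figures assume SD 2.5, a true difference of 0, all 122 per arm analysed, and a 95% interval. The change is worth making because it costs almost nothing and settles in advance which analysis decides the trial.

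**What to change.** In Statistical considerations and analysis:

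- Make the primary analysis of time to functional recovery a linear model of days on arm plus fistula risk, biliary stenting and PDAC diagnosis. Read the arm coefficient and its 95% interval against the 1-day margin, with a robust or bootstrap interval if days are skewed.
- Keep the unadjusted comparison as a sensitivity analysis.
- Limit the logistic regression to the binary 8-week chemotherapy endpoint, adjusted for fistula risk and stenting. Every patient in that sub-cohort has PDAC, so the third factor drops out.

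This changes wording only. The three factors are already recorded for randomisation, the model spends three degrees of freedom, and no patient or visit is added. The change should be made before any comparison by arm is seen.
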